# Effects of a chronotype-adapted diet on weight loss, cardiometabolic health, and gut microbiota: study protocol for a randomized controlled trial

**DOI:** 10.1186/s13063-024-07996-z

**Published:** 2024-02-28

**Keywords:** Chronotype, Diet, Weight loss, Cardiometabolic health, Gut microbiota, Randomized controlled trial

## Abstract

**Background:**

Obesity and its associated health complications have become a global public health concern, necessitating innovative approaches to weight management. One emerging area of research focuses on the influence of chronotype, an individual’s preferred timing for daily activities, on eating habits, weight regulation, and metabolic health. Recent observational studies suggest that the misalignment between an individual’s chronotype and external cues, such as meal timing, may contribute to metabolic dysregulation and obesity, but evidence from intervention studies is still limited. This study protocol describes a randomized controlled trial designed to explore the effects of a chronotype-adapted diet, compared with a diet with a conventional calorie distribution, on weight loss, cardiometabolic health, and gut microbiota composition.

**Methods:**

A total of 150 overweight/obese adults will be recruited for this 4-month parallel-group, randomized, two-arm, open-label, superiority trial with 1:1 allocation ratio. Participants will be randomly assigned to either the intervention group or the control group. The intervention group will receive a low-calorie chronotype-adapted diet with a calorie distribution adapted to the individual chronotype (morning or evening), optimizing meal timing according to their peak metabolic periods. The control group will follow a standardized low-calorie healthy eating plan without considering chronotype. Both diets will have equivalent daily calorie content, adjusted according to gender and starting weight. Anthropometric measurements, body composition, blood, and fecal samples will be obtained from each participant at the beginning and the end of the study. The primary outcome is weight change from baseline. Secondary outcomes are changes from baseline in body mass index (BMI), fat mass, lipid and glycemic profile, fecal microbiota profile, and short-chain fatty acids (SCFAs).

**Discussion:**

The results of this randomized controlled trial have the potential to advance our understanding of the complex interactions between chronotype, diet, body weight, and health outcomes. By providing evidence for personalized dietary interventions based on individuals’ circadian preferences, this research could offer insights into personalized nutrition strategies. Such knowledge could guide the development of innovative dietary interventions to optimize the prevention and management of overweight and obesity, while also improving the risk profile of these individuals.

**Trial registration:**

ClinicalTrials.gov NCT05941871. Registered on 18 May 2023.

**Supplementary Information:**

The online version contains supplementary material available at 10.1186/s13063-024-07996-z.

## Introduction

In recent years, the prevalence of overweight and obesity has reached epidemic proportions [1], posing significant challenges to public health worldwide [2]. The complex interplay between lifestyle factors, including diet, physical activity, and sleep patterns, has been recognized as key contributors to weight management and overall health [3]. However, effective strategies for the prevention and management of overweight and obesity are still limited [3].

An emerging body of evidence suggests that the timing of food intake, in relation to individual chronotype, may be involved in modulating metabolic processes and promoting optimal body weight and cardiometabolic health [4–6]. Chronotype refers to an individual’s preference for activity and sleep patterns during a 24-h cycle [7] and is generally determined based on the scores obtained from validated questionnaires such as the Morningness Eveningness Questionnaire (MEQ) [8]. Early risers, who are preferentially active in the morning, are said to have a morning chronotype, while late risers with more nocturnal activities are said to have an evening chronotype [7]. Research has indicated that chronotype is not merely a preference but is genetically determined and associated with variations in circadian rhythms, hormonal regulation, and metabolic function [9, 10].

The rationale for examining the effects of a chronotype-adapted diet stems from the growing number of studies suggesting that circadian rhythms play a crucial role in metabolic regulation and overall health [11–13]. Disruptions in circadian rhythms, often resulting from modern lifestyle factors such as irregular sleep schedules and food intake, have been associated with adverse health outcomes, including obesity, metabolic syndrome, and alterations in gut microbiota composition [14, 15]. A chronotype-adapted approach involves consuming most calories during the peak period of wakefulness, when metabolic processes are most active, and adapting the timing of meals accordingly for individuals with different chronotypes. A recent clinical study conducted in overweight and obese subjects showed that a chronotype-adapted dietary intervention resulted in greater weight and fat mass loss than a non-adapted intervention, suggesting that aligning mealtimes and macronutrient distribution to an individual’s chronotype may be a promising approach to enhance weight loss efforts [16]. In contrast, several studies have shown that individuals with a misaligned sleep–wake schedule, especially late risers forced into an early-rising routine, experience disruptions in various physiological processes, including alterations in appetite regulation, glucose metabolism, and lipid profiles [12, 17]. These metabolic disorders can ultimately lead to weight gain and an increased risk of cardiometabolic diseases. The composition and activity of the gut microbiota have also been linked to energy metabolism and metabolic health [18]. In this regard, recent investigations have demonstrated bidirectional communication between the gut microbiota and the host’s circadian system, further emphasizing the potential role of chronotype, dietary patterns, and timing in modulating this intricate relationship [15].

Despite the great interest in this topic, most of the studies available to date are observational. Therefore, we propose to conduct a randomized controlled trial to investigate the effects of a chronotype-adapted diet, compared with a diet with a conventional calorie distribution, on weight loss, cardiometabolic health, and gut microbiota composition. Both dietary interventions will be standardized to ensure equivalent daily calorie content, adjusting for gender, and starting weight.

We hypothesize that aligning dietary patterns with the individual inherent biological clock will optimize metabolic processes and promote beneficial changes in gut microbial composition, ultimately leading to improved health outcomes. We also speculate that a chronotype-adapted diet may have a lower dropout rate because these diets are more easily adapted to each patient’s preferences.

## Methods: participants, interventions, and outcomes

### Study design and setting

A 4-month parallel-group, randomized, two-arm, open-label, superiority trial with 1:1 allocation ratio to either intervention or control arms will be conducted at the Unit of Clinical Nutrition of the Careggi University Hospital, Florence, Italy. The study design follows the SPIRIT reporting guidelines [19] (see Fig. 1 and Supplementary file 1).

**Fig. 1 Fig1:**
[figure not shown]
SPIRIT figure reporting the phases of the trial and data collection time points

In the design of the study protocol, there was no direct involvement from the public or patients. While we recognize the growing importance of patient and public involvement in research, for this study, the protocol was developed within the framework of scientific and clinical expertise.

### Participants

A total of 150 overweight and obese females and males aged between 18 and 65 years with a body mass index (BMI) ≥ 25 kg/m^2^ will be included in the study. Exclusion criteria will be the presence of chronic illnesses or unstable conditions that could interfere with the dietary intervention (e.g., cancer, kidney or liver disease, inflammatory bowel disease, cognitive decline, and psychiatric disease); drug therapies that could interfere with the effectiveness of the dietary intervention (e.g., use of corticosteroids, and anti-diabetic drugs); pregnancy or intention to become pregnant in the next 12 months; breastfeeding; current or recent (last 3 months) adoption of a low-calorie diet.

Before starting any research activities, including the initial run-in period, the study investigators will obtain written informed consent from each participant. All subjects must voluntarily agree to participate and will be free to withdraw from the study at any time. Study participants will also be asked for written informed consent to keep the biological samples for future research and to publish the data anonymously.

### Interventions

After a 2-week run-in period, eligible participants will be divided into two groups: the intervention group, which will be given a low-calorie chronotype-adapted diet with a calorie distribution adapted to the individual chronotype (morning or evening), and the control group, which will be given a low-calorie control diet with a standard calorie distribution.

In the intervention group, chronotypes will be assessed according to scores obtained with the Morningness-Eveningness Questionnaire (MEQ) [8]. Participants with a score between 52 and 86 will be classified as morning chronotypes and will receive a morning-adjusted diet, while those with a score between 16 and 51 will be classified as evening chronotypes and will receive an evening-adjusted diet [16]. The daily caloric distribution will be as follows: (1) morning chronotype − 50% of the daily kcal will be administered before lunch and 15% in the second part of the day (specifically: 40% at breakfast, 10% in the morning snack, 35% at lunch, 5% at snack and 10% at dinner); (2) evening chronotype − 15% of the daily kcal will be administered before lunch and 50% in the second part of the day (specifically: 10% kcal at breakfast, 5% in the morning snack, 35% at lunch, 10% at snack and 40% at dinner). The daily caloric distribution in the control group will be as follows: 20% kcal at breakfast, 10% in the morning snack, 35% at lunch, 10% at snack, and 25% at dinner.

Both diets will be hypocaloric with respect to the participants’ energy requirements. Specifically, they will provide 1200 kcal for women and 1400 kcal for men with a body weight < 90 kg at the first visit, and 1400 kcal for women and 1700 kcal for men with a body weight > 90 kg. Furthermore, both dietary profiles will have about 30% of the energy coming from fat, 15–20% from protein, and the remaining 50–55% from carbohydrates (mainly complex). The only difference will be the distribution of calories throughout the day, which will be chronotype-based in the intervention group and standard in the control group. Participants may discontinue the intervention or withdraw from the study for the following reasons: (1) at the request of the participant; (2) if the investigator considers that a participant’s health will be compromised due to adverse events or concomitant illness that develop after entering the study.

To improve adherence to intervention protocols, qualified nutritionists will provide participants with a detailed 1-week menu plan based on their intervention group, with all food ingredients expressed by weight and/or volume, and a handout containing details of the assigned diet with possible substitutions. No meals or supplements will be provided. Participants will prepare their own meals or eat at a restaurant. For both diets, alcoholic beverages will be limited to one per day for women and two per day for men. Participants will be asked not to change their exercise habits during the study. In addition, the use of cortisone therapies, antidiabetic drugs or the use of vitamin supplements, minerals, or products aimed at weight loss will not be allowed during the study. Patients who need to start using these products under a doctor’s recommendation during the intervention period will be excluded from the study. No further arrangements or ancillary assistance will be provided upon completion of the study.

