### Assignment of interventions: allocation

A web-based online randomization procedure will be used to generate the allocation sequence. No adaptive randomization procedures will be performed. The random assignment sequence will be produced and managed by an investigator who will not participate in the recruitment of participants. The order of assignment will be kept secret from the experimenters who will enroll participants or assign interventions. The group assignment will be presented on a folded sheet of paper in a sealed envelope.

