### Statistical analysis

Statistical analyses will be performed using SPSS software for Macintosh (SPSS Inc., Chicago, IL, USA). Data will be analyzed using intention-to-treat and on-treat procedures. The primary outcome (change in body weight) will be analyzed within each group using Student’s *t*-test for paired data. The difference in absolute change (mean value at baseline subtracted from the mean value after the intervention for each subject) will be estimated using the Student’s *t*-test for independent data. Evaluation of distributions and checking for outliers will be performed using histograms and box plots. If appropriate, variables will be logarithmized to normalize the distributions of data. Continuous variables that follow a normal distribution will be summarized using the mean and standard deviations. Categorical variables will be presented in terms of frequencies and percentages. After testing the regression assumption, a general linear model for repeated measurements with adjustments for possible confounding factors will be run to compare the effects of different interventions. Data for the general linear model will be reported as geometric means and 95% confidence intervals. The same analyses will be performed for secondary outcomes. Subgroup analyses will be performed to analyze possible differences in the changes, according to some characteristics of the study population, such as age and gender.

Before starting the data analysis, the level and possible causes of missing data will be investigate using appropriate tables. This information will be used to determine whether the level and type of missing data have the potential to introduce bias into analysis results or substantially reduce the precision of the estimates for the proposed statistical methods. Sensitivity analyses will be performed, based on the assumption that the missing outcomes are the worst or best possible in the different randomization groups. If these show that the conclusions may differ based on the missing values, further multiple imputation will be performed for the missing values. These analyses will consider the results of any losses at follow-up to the extent that they relate to differences in the measured variables (i.e., under the assumption of random missingness). A *P* value < 0.05 will be considered statistically significant.

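### Sex and a 90 kg cut set each participant's calorie level, but the stated between-arm t-test of weight change ignores both: a modest, avoidable loss of precision

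*Protocol article*

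**What the plan says.** Interventions (Protocol article) sets four energy levels. The lower weight class is prescribed "1200 kcal for women and 1400 kcal for men with a body weight < 90 kg at the first visit". For the upper class, the same sentence gives different figures: "1400 kcal for women and 1700 kcal for men with a body weight > 90 kg". The abstract describes the same rule: "Both diets will have equivalent daily calorie content, adjusted according to gender and starting weight". It applies in both arms. Of the two diets, Interventions says: "The only difference will be the distribution of calories throughout the day".

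For the primary outcome, Statistical analysis compares the arms with an unpaired Student's t-test. The sentence that names this test opens: "The difference in absolute change (mean value at baseline subtracted from the mean value after the intervention for each subject) will be estimated using the". The section then adds a general linear model for repeated measurements with "adjustments for possible confounding factors", which are not listed. Age and gender appear only as examples of subgroups.

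The allocation section says "A web-based online randomization procedure will be used to generate the allocation sequence". On adaptive methods it adds: "No adaptive randomization procedures will be performed". It neither names strata nor says that there are none.

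**The concern.** The outcome is weight change, and the protocol sets the calorie level, a direct driver of weight change, by two baseline facts. Energy requirement rises smoothly with weight, but the prescription jumps at 90 kg. Two men of 89 and 91 kg have nearly the same requirement, yet are prescribed 1400 and 1700 kcal. Two such women are prescribed 1200 and 1400 kcal. Expected loss therefore follows a sawtooth in baseline weight, and a straight line in weight cannot represent the step.

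An unadjusted t-test puts all of this into the residual. The standard error is then larger than it need be, and a chance difference between arms in the mix of cells goes uncorrected. At stake is precision, not validity.

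There is also a coding gap. One level is defined below 90 kg and the other above it, so a participant at exactly 90.0 kg on a scale accurate to 0.1 kg (Data collection and management) has no defined level.

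**Working it through.** **Inputs from the Protocol article:** the four energy levels (Interventions); a 1.4% difference, SD 0.4%, 22% loss, power 0.80, alpha 0.05 and 54 per group (Sample size); 150 recruited, 1:1.

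**Assumed, because the documents give no figure:** a mean difference d in weight change between two prescription groups of 0.5% to 2.0% of body weight; a share p of 30% to 50% in one group; a two-sided test.

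1. *Steps.* 1400 − 1200 = 200 kcal/day (women); 1700 − 1400 = 300 kcal/day (men).

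2. *A usable SD.* The stated inputs give n = 2 × [(1.96 + 0.84) × 0.4 / 1.4]² ≈ 1.3, so 2 per group (3 after allowing for loss), not 54. That is a separate matter. Here it means only that the SD must be solved back from 54: SD = 1.4 / [2.80 × √(2/n)]. With 54 × 0.78 ≈ 42 completers the SD is 2.29%; with 54 completers it is 2.60%.

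3. *Share of outcome variance* = p(1 − p)d² / SD². At d = 1.4%:
   - SD 2.29%: 0.25 × 1.96 / 5.24 = 9.3% (p = 0.5); 0.21 × 1.96 / 5.24 = 7.8% (p = 0.3).
   - SD 2.60%: 0.49 / 6.76 = 7.2%; 0.41 / 6.76 = 6.1%.
   - Over d = 0.5% to 2.0% the share runs from about 1% to 19%.

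4. *Power* = Φ[1.4 / (SD × √(2/n)) − 1.96], before and after removing that variance at d = 1.4%:
   - SD 2.29%, 42 per arm: 0.80 rises to 0.83–0.84 (residual SD 2.18% to 2.20%).
   - SD 2.60%, 75 × 0.78 = 58.5 per arm: 0.83 rises to 0.85–0.86 (residual SD 2.50% to 2.52%).

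5. *Chance imbalance.* The SD of the between-arm difference in group share is √[2p(1 − p)/n], which is 7 to 11 points for 75 down to 42 per arm. Multiplied by 1.4%, a one-SD imbalance moves the contrast by 0.10% to 0.15% of body weight. This is the loss in step 4 seen from another side, not an addition to it.

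6. *Does the cell add to sex and weight?* I simulated with assumed inputs: 70% women; weight mean 90 kg, SD 14 kg; requirement 1900 kcal (women) and 2400 kcal (men) at 88 kg, slope 10 to 20 kcal/kg; 7,700 kcal/kg; 120 days; 50% or 100% adherence; residual SD 2.3 to 3.5 kg. Weight plus cell cut residual variance by about 9% or more against the unadjusted comparison. Beyond linear weight plus sex, the cell cut it by a further 3% to 6% at half adherence, and by about 10% to 20% only at full adherence.

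7. *The jump at 90 kg against the difference between whole classes.* With mean 90 kg and SD 14 kg, the classes differ in mean weight by 2 × 0.798 × 14 = 22.3 kg, hence in requirement by 223 to 447 kcal. The average step is 0.7 × 200 + 0.3 × 300 = 230 kcal.
   - At 10 kcal/kg the net difference is −7 kcal, or about 0.1 kg or less over 120 days.
   - At 20 kcal/kg it is 217 kcal the other way: 217 × 120 / 7,700 = 3.4 kg at full adherence and 1.7 kg at half, with the heavier class losing more.

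**The case against.** The strongest reply is that this is detail left out, not an error. An article commonly leaves strata and covariate lists to the full protocol or analysis plan, and sex and starting weight are obvious candidates for the adjusted general linear model. That stands for the model, whose covariates may well include both. It does not answer the t-test, which the article itself states for the between-arm difference and which adjusts for nothing.

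A second reply is that the gain is small once sex and baseline weight are in a model. That also stands: step 6 gives only a few per cent more at half adherence. The 90.0 kg gap, too, is a drafting slip that touches few people and both arms alike.

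A reader might go further in three ways that the documents do not support:
- *That the step is as large as the effect sought.* No kilogram effect of 200 to 300 kcal/day is given. At 7,700 kcal/kg over 120 days, with 25% to 100% of the step realised, it is 0.8 to 4.7 kg, against 1.4% of 90 kg = 1.26 kg. A difference between participants is also not comparable with a difference between arms.
- *That chance imbalance in weight class shifts the estimate by the imbalance times the jump at 90 kg.* The right multiplier is the difference between whole classes, which step 7 shows can be near zero or of opposite sign.
- *That the allocation is declared unstratified.* The article is silent on strata.

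**Conclusion.** The point holds as a matter of efficiency. The protocol makes sex and first-visit weight class predictors of its primary outcome, and the between-arm test that it states leaves them in the error. The energy rule is identical in both arms and randomization balances the cells in expectation, so the treatment estimate is not biased.

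The loss is modest: about 6% to 9% of outcome variance and 2 to 4 power points if the groups differ by 1.4% of body weight, and less or more as that difference is smaller or larger. This rests on an SD solved back from 54 per group and on an assumed group difference; neither figure stands in the documents. The step sizes, the unadjusted test and the undefined value at 90.0 kg come straight from the text.

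**What to change.** State the primary between-arm analysis of weight change as a linear model with arm, baseline weight and the prescription cell (sex by first-visit weight class, four levels), all prespecified. Use the same terms for BMI and fat mass. Fix this before outcomes are examined by arm, and report the numbers per cell and arm.

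Reconcile the below-90 and above-90 wording so that a weight of exactly 90.0 kg falls in a defined cell. Which level applies is for the investigators to settle.

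The cost is four degrees of freedom beyond the t-test (one for baseline weight, three for the cell), leaving 117 − 6 = 111 rather than 115 with 150 × 0.78 = 117 completers. The data are already collected. No change to the allocation is proposed: with completion scheduled for 30 April 2024 and a four-month intervention, randomization would have ended by about the close of 2023 if the schedule held.

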### Outcomes

The primary outcome is weight change from baseline. Secondary outcomes are (1) body mass index (BMI) and fat mass change from baseline; (2) lipid and glycemic profile change from baseline (total cholesterol, LDL-cholesterol, HDL-cholesterol, triglycerides, fasting glucose); and (3) fecal microbiota profile and short-chain fatty acids (SCFAs) change from baseline. Body weight will be measured as a unique and established quantitative primary outcome, while assessment of body composition, biochemical profile, and gut microbiota will provide information on the cardiometabolic status of participants. The metric used will be the change in mean values from the beginning to the end of each dietary intervention.

